# 1. INTRODUCTION AND RATIONALE

Dementia is a condition that is characterised by progressive dependency. In the advanced stages dementia demands either professional or informal care or a combination of these two. Worldwide dementia prevalence is predicted to rise from 35.6 million in 2010 to 65.7 million in 2030.(Ferri et al. 2009)

In most developed countries dementia care is already at the top of the list of conditions weighing heaviest on health care expenditures and growing fastest.

In gate keeping primary health care systems like the Netherlands, FPs play a pivotal role in the recognition and diagnosis of dementia and in linking or referring patients and caregivers to secondary dementia care (such as memory clinics and case management programs) and other community services. Although both dementia patients and informal caregivers are likely to benefit from earlier recognition and diagnosis of the condition(Boise et al. 2004;Sandholzer et al. 1999), dementia is still often diagnosed late in the disease process(Boise et al. 2004;Bradford et al. 2009;Meerman et al. 2008). Educational interventions aimed at FPs have the potential to raise the rate of diagnosis(Downs 2006). Additional coaching of FPs and collaboration of FPs with trained health care nurses, specialised in dementia diagnosis and management results in better adherence to diagnostic guidelines and improved rates of disclosure and education of patients and caregivers(Perry et al. ;Perry et al. 2008).

At present, management of dementia patients and their informal carers in primary care is predominantly following demands rather than being provided proactively. Adherence to dementia guidelines is low(Hinton et al. 2007;Wenger et al. 2003) and although FPs consider assessment of care needs of patient and caregiver important, this is often not achieved in daily practice(Schoenmakers et al. 2009;Van Hout et al. 2000). FPs acknowledge that behavioural problems, an important predictor of caregiver burden, are treated suboptimally (Hinton et al. 2007). Nevertheless, they appear to be poorly informed about the content of community support services and only a small proportion of North-American FPs refer to such services(Cody et al. 2002;Schoenmakers et al. 2009;Yaffe et al. 2008).

With the upcoming dementia epidemic, we consider it important to structurally improve management of dementia in primary care, with assessment of care needs of patients and caregivers, composing (and revising) of care plans for both patients and caregivers and referral to community services or regional care providers according to their needs. Previous research has shown that multifaceted interventions, such as education and support of FPs and building strong collaboration amongst dementia care providers and services in a region are potentially effective.

Vickrey et al. showed significant effects on quality of care and caregiver outcomes of such an intervention. They implemented at the primary care level a structured assessment by a casemanager, algorithms linking specific care management actions to assessment results and interorganizational care coordination and referral protocols(Vickrey et al. 2006). Reuben et al also attempted to improve dementia care by means of a multifaceted intervention(Reuben et al. 2003). They failed at their first attempt but learned that physicians perform better at medical tasks then at counselling and education. Furthermore physicians are often unaware of various community services and relatively inexperienced in the treatment of behavioural symptoms. The authors collaborated with FPs to tailor the intervention more to the their specific perceived demands and needs and succeeded to improve some aspects of quality of care and to improve interdisciplinary collaboration(Reuben et al. 2010). Where Perry et al. did show effects of their multifaceted intervention on quality of the diagnostic process, they did not find significant effects on the quality of the follow-up care/long term care process for patient and caregiver(Perry et al. 2008).

FPs indicate they need (and welcome) support to improve care (Cody et al. 2002;Van Hout et al. 2000). Previous research demonstrated that nurses are better at managing care then at diagnosing dementia. Particularly management of behavioural symptoms is perceived to be difficult(Bryans et al. 2003). Callahan showed that collaboration within an interdisciplinary team led by an advanced practice nurse had significant effects on medication usage and on behavioural and psychological symptoms of dementia patients(Callahan et al. 2006).

Adequate management of behavioural and psychological problems is however time consuming and requires specific expertise(Chenoweth et al. 2009). This task may therefore be more suitable to be performed by specialised case managers or mental health workers.

In conclusion: Both the recognition and diagnosis of cognitive impairment and the care for home dwelling persons with dementia and their informal carers need to be improved. Potentially effective strategies have been identified. These interventions were however not effective in all studies. The collaborative team of FP and practice nurse can play an important part in the *diagnosis* of dementia, the *assessment* of needs of persons with dementia and their caregivers and in the *provision* and *coordination* of stepped dementia care. FPs and nurses both have their specific strengths and weaknesses that need to be taken into consideration in the division of tasks. This collaborative model deserves further development and evaluation as it is potentially a high quality, cost-effective complement to secondary care dementia services.

# 2. OBJECTIVES

Our primary objective is to estimate whether a multifaceted intervention including collaboration of FPs and trained practice nurses in the diagnosis of mild cognitive impairment (MCI) and dementia and in subsequent management improve the quality of the diagnostic process and the quality of care.

Secondary objectives are to investigate:

a) Whether this intervention improves the general wellbeing of dementia patients and their informal caregivers;

b) The accuracy of the FPs’ cross-sectional classification of the cognitive status of all patients ≥ 65 years and c) whether the intervention is cost-effective

d) Success and failure factors of this intervention.

# 3. STUDY DESIGN

To estimate the effects of the intervention on quality of the diagnostic process, quality of care and on patient and caregiver wellbeing, a stepped wedged cluster RCT design over 24 months will be used. Stepped wedged means that all practices eventually apply the intervention but the starting point per practice is randomised in early and late starters (>12 months). This design is also used for the cost-effectiveness analysis (Figure 1).

To study the accuracy of the FPs cognitive classification we will use a classical Diagnostic Test Accuracy Design. The cross sectional classification of the FP is compared to a reference standard diagnosis. Both patients initially classified with (N~312) and without (N~100) cognitive impairment according to the FPs are recruited. Equal numbers of patients will be randomly sampled per PCP.

For the evaluation of the implementation process, semi structured interviews and focus groups are held with FPs, practice nurses, key representatives of local dementia services as well as with couples of demented persons and their informal caregivers.

# *A flow chart can be included to give a overview of the procedures that subjects will undergo in the course of research.>*

# STUDY POPULATION

## Population (base)

Cluster RCT: FPs indicated on a list of all their elderly patients (age ≥ 65 years) those patients whom they thought might be cognitively impaired, based on their general impression of patients or their ‘gut feeling’. They could make use of the medical records but did not make use of screening instruments for this classification.

Patients within the primary care practices and their informal carers are eligible for study participation if they fulfil the following criteria:

## Inclusion criteria

1. Patients are classified as possibly cognitively impaired or possibly having dementia based on FPs’ general impression.
2. A primary informal caregiver can be identified. Definition primary informal caregiver: the person who has a central role in (and takes responsibility for) the care of an, independently living, disabled relative or partner.

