## Exclusion criteria

1. Patients allready diagnosed with dementia.
2. Patient or (if present) caregiver terminally ill.
3. Permanent admission of the patient to a nursing home expected within 6 months.
4. The patient is not/no longer sufficiently capable of understanding spoken language or expressing him- or herself.

Diagnostic Test Accuracy Study: In order to also get information about the negative predictive value of the FPs cognitive classification, an additonal sample will be drawn of patients FPs classified as ‘no signs of cognitive impairment’ (Figure 2).

The study population for the process evaluation of succes and failure factors of the intervention consists of FPs and practice nurses in the intervention group. In addition, a random selection of patients and caregivers in the intervention group is invited to participate in a semi-structured interview.

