## Sample size calculation

In order to come to a sample size that would allow showing significant differences in quality of care, in wellbeing and in numbers of new dementia diagnoses we performed several power calculations:

Quality of care:

The primary outcome is the difference in total score on a set of quality indicators (QIs) after 12 months between intervention and control group. Perry et al. found a mean (crosssectional) concordance to the total set of 45.3% (SD 30.4). A serial measurement is not yet done with this set of QIs.

For this study we expect an increase in concordance in the intervention group of around 1.5 times the baseline scores. In other words; an added 22,5% concordance with the total set of QIs is considered as clinically relevant. We based out powercalculation on the method described by Kerry et al.(Kerry and Bland 1998). To be safe we assumed a somewhat larger within cluster SD of 35 than Perry et al. found. Based on research of Campbell et al on ICCs in primary care research we assumed a between cluster SD of 3(Campbell et al. 2005).

With an α of 0.05 and β of 0.90, a sample size of 5 clusters per arm and 72 patients per arm is required to show a statistically significant and clinically relevant difference in quality of care.

Caregiver wellbeing:

We chose the GHQ12 as a meausure of caregiver mental health as the most important patient and caregiver wellbeing measure. We expect to find results after a period of 12 months on this outcome. We based our sample size for the GHQ 12 on a study of Diaz et al . in 2008. They report a significant difference in GHQ 12 decline between intervention and control group. The average difference in decline was 2.2 points in a period of 6 months. Based on their SDs we (conservatively) estimated SDs in the control- (4.3) and interventiongroup (3.6). Based on the formula: √(SDbaseline2 x SDfollow-up2).

A paired t-test for average difference with unequal variance shows that assuming an equal distribution over intervention and controlgroup,a desired power of 90%, and an alpha of 0.05 we need to include 57 caregivers per group in order to find significant and clinically relelvant results (SASsoftware). Estimating that about half of patients will have an informal caregiver and that about 20% will be lost to follow-up in the first year and adding 10 % for clustering resulted in a desired sample of 156 patients per arm.

Number of new dementia diagnoses in 12 months:

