We based this calculation on a previous study on an educational intervention to improve the number of dementia diagnoses in primary care(Perry et al. ). Perry et al. conducted a cluster RCT design in which they asked 105 FPs to select 5 patients in whom they suspected cognitive impairment. FPs collaborated with a practice nurse in diagnosing dementia. In the intervention group, dementia was diagnosed in 49.1% (130 new diagnoses in 265 patients at risk) of these patients, in the control group in 14.8% (20 new diagnoses in 135 patients at risk) of these patients, after one year. Using the probabilities of Perry et al. and assuming a power of 90%, 20% loss to follow-up and adding 10% for clustering within practices resulted in a desired sample of 55 patients per arm.

Diagnostic accuracy of FPs’ classification at baseline

The diagnostyic accuracy is expressed in the positive and negative predictive value of the FPs at baseline. When we include 312 patients, initially classified by the FPs as cognitive impaired as well as and100 patients initially classified with no cognitive impairment, we reach a confidence interval of 17.9% around the point estimate, assuming a prior positive predictive value of 30%.

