## Study procedures

Subjects will not undergo any new or experimental treatment in the course of this study. Their providers will be trained to deliver care (both the process of diagnosis, disclosure and psychoeducation and the process of follow-up care management and support) in closer concordance with current guidelines. Care will become more structured both at the level of the PCP and within the region. For the subjects this will presumably result in an earlier and more thorough assessment of their care needs and earlier intervention or referral. No subjects will be withheld from treatment. We aim to introduce the intervention also in the control group. Because of feasibility the intervention will be introduced in this group one year later.

*Eligibility*

The researchers will assess eligibility of all patients for the study that were diagnosed with dementia. Before approaching potential participants, FPs will go through the list of potential participants to see whether there are any other contraindications, besides the predefined exclusion criteria, to study participation of these persons.

*Recruitment*

Subjects will be informed about the study by means of an invitational letter from their FP and an information leaflet with detailed information about the study: aim of the study, what participation means for participants, freedom to not participate or to end participation at any time without having to give a reason, etc. Subjects are encouraged to discuss the matter with friends or relatives or with their FP. Some subjects may not want to be contacted about the study. They can communicate this by returning a form by post: on this form subjects can indicate that they are not interested to participate in the study and that they do not want to be contacted. A return envelope is provided. (letter and information leaflet are added to this protocol as separate documents)

If subjects do not object, they are contacted by telephone by one of the researchers. Additional clarification about the study is provided, if needed. Subjects are asked whether they are interested to participate in the study. If this is so, an appointment will be made for obtaining informed consent and for the baseline interview.

*Informed consent*

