**Control group**

8 PCPs

- Outcomes in patients with a baseline diagnosis MCI or dementia on the CAMCOG and their informal caregiver

(n ~ 156)

- Patient and caregiver characteristics and outcomes (n =156)

- CAMCOG (n =156)

- CAMCOG (n = 156)

- Quality of care indicators, diagnostic (N=156) & management indicators in patients with dementia (n ~ 50)

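### Entry criterion 2 requires an informal caregiver while the sample size assumes that half of patients have none, and the population for the wellbeing question (goal 3) is not fixed consistently

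*Protocol*

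**What the plan says.** **Caregiver.** Protocol 4.2, criterion 2, lists as a condition of entry that "A primary informal caregiver can be identified". Section 4.3, exclusion 2, reads "Patient or (if present) caregiver terminally ill", which allows for patients without one. Section 4.4 sizes the GHQ-12 comparison from 57 caregivers per group, "Estimating that about half of patients will have an informal caregiver" and that "about 20% will be lost to follow-up in the first year"; "adding 10 % for clustering resulted in a desired sample of 156 patients per arm".

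**Who is screened.** Sections 4.1 and 4.2 define the trial population as patients whom the FP suspects of cognitive impairment, and exclusion 1 removes those with an existing dementia diagnosis. Under Eligibility, Section 7.3 says: "The researchers will assess eligibility of all patients for the study that were diagnosed with dementia".

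**Goal-3 population.**
- Research question 3 in the Summary concerns patients diagnosed with dementia or MCI and their relatives. Secondary objective a (Section 2) speaks of dementia patients only.
- Figure 2 has a box in each arm headed "Outcomes in patients with a baseline diagnosis MCI or dementia on the CAMCOG and their informal caregiver", printed with n ~ 156. A second box in each arm shows patient and caregiver outcomes with n = 156. A third expects about 50 patients with dementia per arm for the management indicators.
- Section 4.4 sizes the accuracy study "assuming a prior positive predictive value of 30"%.
- Section 9.3 compares the two conditions on goals 1 to 3 with no such restriction, and labels the analysis of patients with a baseline CAMCOG below 86 post hoc.
- Appendix 3 lists CAMCOG at baseline and 12 months, with a footnote confining it to the intervention arm. Figure 2 shows it in both arms.

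**The concern.** An entry criterion is applied practice by practice, so it must agree with the calculation that sets the sample. Here the two cannot both hold. If a caregiver is required, doubling the sample for patients without one has no purpose. If one is not required, criterion 2 excludes patients whom the design counts on.

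The literal reading reaches beyond the caregiver outcomes. New diagnoses (goal 1), quality of care (goal 2) and the predictive value of the FP's classification (goal 4) can be studied in patients without a caregiver. Some quality indicators mention the caregiver (items 9, 11, 15 and 23 in Appendix 2), but the set as a whole does not require one. Dropping these patients would narrow the population for three of the four questions and put pressure on recruitment.

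The goal-3 inconsistency matters for a different reason. GHQ-12 is the outcome that drives the 156 per arm, and its power depends heavily on whether all sampled patients or only the cognitively impaired ones are analysed. A population that appears in a research question and in the flow chart should not also be labelled post hoc, because that leaves the choice open until the data are seen.

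**Working it through.** **1. Reproducing the 156.** Inputs from Section 4.4: 57 caregivers per group, half of patients with a caregiver, 20% loss, 10% added for clustering.

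57 / 0.5 / 0.8 x 1.1 = 156.75, against 156 stated. The half-with-caregiver assumption is therefore built into the figure. With every patient having a caregiver: 57 / 0.8 x 1.1 = 78.4, about 79 per arm.

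**2. Criterion 2 applied literally.** Figure 2 lists 650 patients with possible impairment and samples 312. On the protocol's own 50%: 650 x 0.5 = 325 eligible, before any other exclusion. Sampling 312 would need 312 / 325 = 96% of them.

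**3. Size of the restricted goal-3 population.** Section 7.1 defines the accuracy reference as a CAMCOG diagnosis of dementia or MCI, so the 30% predictive value is the assumed CAMCOG-positive share among suspected patients: 156 x 0.30 = 46.8 per arm. Figure 2 expects about 50 per arm with dementia alone (50 / 156 = 32%). The two figures nearly agree, but neither is near 156.

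**4. GHQ-12 power in the possible populations.** Inputs from Section 4.4: difference 2.2, SDs 4.3 and 3.6, alpha 0.05, 20% loss.
- Caregivers analysed per arm: n = 156 x positive share x caregiver share x 0.8.
- Effective number: m = n / 1.1, taking the 10% for clustering as the design effect.
- Standard error: sqrt((4.3² + 3.6²) / m) = sqrt(31.45 / m).
- Power: noncentral t with noncentrality 2.2 / SE and Welch degrees of freedom.

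Example: 156 x 0.30 x 1 x 0.8 = 37.4; m = 34.0; SE = 0.961; noncentrality 2.29; two-sided power 61.6%.

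| Population | Share with caregiver | n per arm | Two-sided | One-sided |
|---|---|---|---|---|
| All sampled | half | 62.4 | 83.4% | 90.2% |
| All sampled | all | 124.8 | 98.6% | 99.4% |
| 30% positive | half | 18.7 | 34.8% | 47.5% |
| 30% positive | all | 37.4 | 61.6% | 73.2% |
| 50% positive (assumed) | half | 31.2 | 53.6% | 66.2% |
| 50% positive (assumed) | all | 62.4 | 83.4% | 90.2% |
| 70% positive (assumed) | half | 43.7 | 68.5% | 79.0% |
| 70% positive (assumed) | all | 87.4 | 93.5% | 96.7% |

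**5. Why both columns.** Section 4.4 does not state sidedness. With the same inputs and no clustering, 57 per group gives 90.3% power one-sided and 83.5% two-sided; 90% two-sided needs 70 per group. The stated 57 therefore fits a one-sided 0.05. That is a separate matter, and the one-sided column isolates the effect of the population.

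**6. If all sampled patients are analysed.** The first two rows assume the full 2.2 points in every caregiver, but the Summary offers collaborative care only after an MCI or dementia diagnosis. Assume 30% benefit fully and the rest not at all: mean effect 0.3 x 2.2 = 0.66, two-sided power 14% at n = 62.4 and 24% at n = 124.8. If the other 70% gain half: 0.66 + 0.7 x 1.1 = 1.43, power 48% and 77%.

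**The case against.** Several points on the other side stand.

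- **A reader might infer that the GHQ-12 analysis will hold only about 19 caregivers per arm.** The protocol does not say so. That figure joins the CAMCOG restriction, the 30% from the accuracy calculation and the half-caregiver share, which no section combines, and it sets criterion 2 aside. Figure 2 also shows outcomes in all 156 per arm. Its layout is lost in the available text, so which box belongs to which visit cannot be recovered.
- **A reader might correct the n ~ 156 to 47.** That would put MCI-or-dementia below the roughly 50 that the same figure expects with dementia alone.
- **A reader might conclude that goal 3 should simply be analysed in everyone.** Research question 3 and secondary objective a point the other way, and step 6 shows that the cost in power could be large.
- **A reader might set the two-sided 83% against the stated 90% and blame the population.** On the one-sided basis that yields 57, the same 62 caregivers give 90%.
- GHQ-12 is a secondary outcome. The primary outcome, quality of care, is sized at 72 per arm against 156 planned, and enforcing criterion 2 would raise caregiver power rather than lower it.
- The eligibility sentence in 7.3 looks like a drafting slip, since the Summary and Sections 4.1 to 4.3 agree on the population.

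None of this reconciles criterion 2 with exclusion 2 and the sample-size text, or settles who is analysed for goal 3.

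**Conclusion.** The protocol contradicts itself on whether a caregiver is needed for entry, and the planned 156 per arm stands only if one is not (about 79 if one is). Literal use of criterion 2 would remove about half of the suspected patients from goals 1, 2 and 4; this rests on the protocol's own 50% applied to the 650 listed.

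The goal-3 population is also stated inconsistently, and the n ~ 156 in the restricted Figure 2 box is the whole arm, not the expected number of CAMCOG-positives. If the restriction is intended, GHQ-12 power at 30% positive is about 62% two-sided (73% one-sided) with caregivers for all and 35% (48%) with caregivers for half, under 20% loss and a 1.1 design effect. A larger positive share improves this: at an assumed 50% positive with caregivers for all, power returns to 83% (90%). The documents do not show that the restricted analysis is the planned one, so low power is a conditional consequence and not an established defect.

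Severity: should be fixed. The primary outcome's power is not at risk.

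**What to change.** 1. Make criterion 2 a condition for the caregiver outcomes only, not for patient entry. This agrees with exclusion 2 and with the arithmetic in Section 4.4.
2. In the Eligibility paragraph of 7.3, describe those screened as patients classified by the FP as possibly cognitively impaired, in line with Sections 4.1 to 4.3.
3. Name one goal-3 population in advance and use it in research question 3, objective a, Figure 2 and Section 9.3. Any other population becomes a pre-specified supporting analysis, and the post hoc label goes.
4. Correct the n in the restricted Figure 2 box to the expected number of CAMCOG-positives, about 50 or more per arm, with the assumed share stated.
5. If the restricted population is chosen, restate the GHQ-12 power for it, giving the positive share, caregiver share and sidedness. If all sampled patients are chosen, state the effect assumed in patients without MCI or dementia.
6. Reconcile the Appendix 3 CAMCOG footnote with Figure 2. Without CAMCOG in the control arm, a CAMCOG-defined population cannot be formed there.

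The cost is an amendment to one criterion, one sentence, one figure, one footnote and the goal-3 wording. If the footnote is what is meant, measuring CAMCOG in controls would add fieldwork; Figure 2 already shows it there.
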